### Statistical analysis

All statistical analysis will be performed by a statistician blinded to treatment.

We choose a superiority study design, with the assumption that treatments are equivalent and set out to test this hypothesis. The primary outcome of complications will be analysed by proportional analysis (odds ratio). Continuous secondary outcomes will be analysed by ANOVA. This study is not powered to discriminate between treatments in terms of DASH and PRWE given the MCID (95% confidence interval) is 10 [5–15] and 14 (8–20), respectively [14].

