## Methods/design

### Trial design

This study is a single centre randomised trial. It has a parallel group design and is stratified by surgeon. Trial admission and randomisation will occur preoperatively.

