### Randomisation and blinding

Block randomisation with stratification by surgeon will be used to ensure equal distribution of participants and size of each treatment group in the event that recruitment goals are not achieved. Eligible patients are randomised 1:1 to TWA with CMCJ arthrodesis and spanning plate or TWA without CMCJ arthrodesis with non-CMCJ spanning plate. The randomisation sequence is concealed and administered by an independent non-clinical staff member of the Trauma and Orthopaedic Research Unit at the Canberra Hospital. Letters are then allocated to participating surgeons containing the concealed treatment allocation. In this way the surgeon cannot influence the type of intervention; and the participants, clinical and research staff are blinded.

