### Primary outcome

The primary outcome is complication within the 12-month post-operative period. These complications are defined in Table 2. Non-union will be assessed at the radiocarpal, midcarpal and carpometacarpal joint (if arthrodesed) by CT.

**Table 2 Tab2:** Complications will be defined to include the following

Wound dehiscence	
Infection: superficial (treated with antibiotics alone) and deep (requiring surgical debridement and antibiotics	
Fracture: in the perioperative period and in the follow up period	
Non-union: recorded radiocarpal, midcarpal and carpometacarpal joint and defined as absence of bridging bony trabeculae with no interval change over 3 months	
Hardware breakage: plate or screw, managed operative or non-operatively	
Tendon rupture	
Tendon irritation: requiring treatment	
Complex regional pain syndrome: defined according to Budapest criteria	
Nerve injury: operatively or not operatively managed	
Other: medical and surgical	

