### Sample size

This study is powered to detect a difference in the rate of complications at the CMCJ. Based on reported complications at the CMCJ in the literature and assuming alpha = 0.05, beta = 0.2 and allowing for 20% drop out, it is expected that 120 participants will be needed to discriminate between the interventions. We plan to recruit patients for this study over 3–4 years.

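### Randomisation is stratified by surgeon, but the analyses named in the protocol do not include surgeon; if run as worded they are valid but conservative to the extent that surgeons differ

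*Protocol article*

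**What the plan says.** The protocol article describes the design twice. Under Trial design: "It has a parallel group design and is stratified by surgeon". Under Randomisation and blinding: "Block randomisation with stratification by surgeon will be used to ensure equal distribution of participants and size of each treatment group", with 1:1 allocation. The reason given there is equal distribution of participants and equal group size should recruitment fall short.

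The endpoint is binary: "The primary outcome is complication within the 12-month post-operative period". The analysis is given in one sentence under Statistical analysis, "The primary outcome of complications will be analysed by proportional analysis (odds ratio"), and the continuous secondary outcomes are assigned to ANOVA. No stratum, covariate or model is named for either. The words crude, unadjusted and unstratified do not appear.

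Under Sample size the plan works from "assuming alpha = 0.05, beta = 0.2 and allowing for 20% drop out" and concludes that "it is expected that 120 participants will be needed to discriminate between the interventions". It gives no event rates. The trial is described as multi-surgeon, but the number of surgeons is not stated.

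**The concern.** The section names methods, and its wording reads most naturally as a comparison of two proportions from a single 2x2 table. That does not follow the randomisation. Stratified blocks force the arms to be balanced within each surgeon, so differences between surgeons drop out of the true sampling variance of the treatment comparison. An unstratified standard error still contains them. If risk differs by surgeon, the intervals are then too wide, the test rejects less often than its nominal level under the null, and power is lost.

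There are reasons to think surgeon could matter here. Technique may differ, and under Outcome assessment and Data collection the treating surgeon records peri-operative complications and post-operative data. Some items in Table 2, such as tendon irritation needing treatment and the open category of other complications, involve judgement. Non-union is less exposed, because an independent radiologist assesses union. At stake is some power in a small trial, not a false positive.

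**Working it through.** **Inputs from the protocol article.** Blocked 1:1 randomisation stratified by surgeon; binary endpoint at 12 months; alpha 0.05 (sidedness not stated), power 0.80, dropout 20%, N = 120.

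**Inputs assumed, because the document does not give them.** Two-sided testing; 3 to 8 surgeons of equal size; a normal surgeon effect on the logit scale with SD from 0 to 1.5; reference risks of 10%, 20% and 30% with within-surgeon odds ratios of 4.36, 3.3 and 3.2.

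**1. The plan's own figure.** 120 x (1 - 0.20) = 96 evaluable, or 48 per arm. Without event rates, 120 can be neither confirmed nor refuted. From

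n per arm = [1.96 sqrt(2 p(1-p)) + 0.84 sqrt(p1(1-p1) + p2(1-p2))]^2 / (p1-p2)^2, with p the mean of p1 and p2,

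the pair 30% vs 58% gives [1.96 x 0.702 + 0.84 x 0.673]^2 / 0.28^2 = 3.77 / 0.0784, or about 48. Pairs near 5% vs 25%, 10% vs 33% and 20% vs 47% also fit. The assumed odds ratios were chosen near this region, so power at SD 0 is close to 80%.

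**2. Why the direction is fixed.** With surgeon-specific risks p_k and overall risk P, and equal strata,

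P(1-P) = mean of p_k(1-p_k) + variance of p_k.

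The unstratified variance uses the left side. Under within-surgeon balance the true variance uses only the first term on the right. The excess is the variance of p_k, which is zero if surgeons do not differ.

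**3. Size.** Each scenario had 20,000 simulated trials of 96 patients, balanced 1:1 within surgeon. The unstratified two-proportion test was compared with the Cochran-Mantel-Haenszel (CMH) test stratified by surgeon. Simulation error (1 SE) is about sqrt(0.05 x 0.95 / 20,000) = 0.15 points for type I error and sqrt(0.75 x 0.25 / 20,000) = 0.3 points for power. Two of the settings:

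| Setting | SD | Type I, unstratified | Type I, CMH | Power, unstratified | Power, CMH | Gain (points) |
|---|---|---|---|---|---|---|
| 20%, OR 3.3, 4 surgeons | 0 | 5.1% | 4.8% | 76.7% | 75.8% | -0.9 |
| | 0.5 | 5.0% | 5.1% | 74.3% | 75.0% | 0.7 |
| | 1.0 | 4.1% | 5.1% | 65.4% | 69.8% | 4.4 |
| | 1.5 | 3.3% | 5.0% | 54.0% | 64.1% | 10.1 |
| 30%, OR 3.2, 8 surgeons | 0.5 | 4.5% | 4.8% | 75.8% | 76.8% | 1.1 |
| | 1.0 | 3.5% | 4.8% | 66.0% | 71.5% | 5.4 |
| | 1.5 | 2.2% | 4.6% | 52.7% | 64.9% | 12.2 |

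Only the difference between the two power columns is the cost of leaving surgeon out. Both columns fall as SD rises, and stratifying does not recover all of that.

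Across all settings:

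| SD | Gain from stratifying (points) | Type I, unstratified |
|---|---|---|
| 0 to 0.3 | about 0, down to -1 | about 5% |
| 0.5 | 0 to 1.1 | 4.5% to 5.7% |
| 1.0 | 2 to 5.4 | 3.5% to 4.9% |
| 1.5 | 6 to 12 | 2.2% to 4.1% |

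The CMH test stayed at about 4.6% to 5.4%. A separate simulation with a median-surgeon risk of 25%, OR 3 and 4 to 8 surgeons agrees: power 69% vs 70% at SD 0.5, 60% vs 65% at SD 1.0, and 47-49% vs 58-59% at SD 1.5.

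**4. How plausible each SD is.** With a median risk of 25%, logit(0.25) = -1.10, and the central 95% range of surgeon risk is expit(-1.10 +/- 1.96 SD): about 11% to 47% at SD 0.5, 4% to 70% at SD 1.0, and 2% to 86% at SD 1.5. The last is extreme for one centre whose surgeons, under Intervention, all have subspecialist hand training and know both procedures.

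**The case against.** The best reply is that the article does not say the odds ratio is unstratified. A Mantel-Haenszel estimate or a logistic model with surgeon as a factor also gives an odds ratio, and ANOVA can include surgeon. An analysis plan, not shown here, may say so, and stratum adjustment is commonly settled there. This stands to the extent that a reader might infer that the plan has fixed a crude analysis and discards surgeon; the text does not establish that. It does not remove the point, because the article names its methods and, read plainly, they do not match the randomisation it describes.

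Three further objections stand:

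- A reader might infer that the trial stratifies because complication rates differ by surgeon. The Randomisation and blinding section gives balance and group size as the reason.
- An unstratified odds ratio lies nearer 1 than the within-surgeon one when surgeon is prognostic. That is non-collapsibility, not bias; the marginal odds ratio is a legitimate target in a randomised trial.
- Stratifying is not free. Surgeons with no events, or with evaluable patients in one arm only, contribute nothing to the Mantel-Haenszel estimate. The simulations used equal strata and exact balance, so they did not test this.

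**Conclusion.** The point holds in conditional form. Surgeon is the stratification factor and is absent from the named analyses. If those are run without strata, the comparison remains valid, with no material excess of false positives, but it is conservative in proportion to how far surgeons differ. Under the assumptions above, the power loss is about 0 to 1 point at SD 0.5, 2 to 5 at SD 1.0 and 6 to 12 at SD 1.5.

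The stronger conclusion that a reader might draw, that the trial will lose power, is not supported: the number of surgeons, their variation and the event rates are all unstated, and with similar surgeons the loss is nil. The case for acting rests on matching the analysis to the design at almost no cost and on settling the choice before outcome data are seen.

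**What to change.** Add to the Statistical analysis section that the primary odds ratio, with 95% CI, is the Mantel-Haenszel estimate stratified by surgeon; that surgeons below a stated number of patients are pooled by a rule fixed in advance; and that surgeon is a factor in the ANOVA models for continuous outcomes. The pooling rule should depend on patient numbers only, not on events by arm. If an analysis plan already says this, the two texts only need to agree.

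The cost is a sentence or two and no new data. The downside is up to about 1 point of power if surgeons hardly differ, plus the need for the pooling rule where strata are sparse.

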**Method:**

A single centre randomised clinical trial including 120 adults with end-stage isolated wrist arthritis will be performed to compare TWA with and without the CMCJ included in the arthrodesis. The primary outcome is complications in the first post-operative year. Secondary outcomes are Disabilities of the Arm, Shoulder and Hand (DASH) score, Patient Rated Wrist Evaluation (PRWE) and grip strength measured at 1, 2 and 5 years. Late complications, return to work and satisfaction will also be recorded.

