### Baseline data

A timeline for assessment is given in Fig. 1. Initial pre-operative assessment will obtain data on comorbidities, function, clinical assessment of pain at the CMCJ and radiographic assessment with x-ray and computer tomography (CT). Patient reported outcome measures including the DASH and the PRWE will also be administered.

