### Secondary outcomes

Secondary outcomes will include changes from baseline DASH and PRWE. Secondary outcomes will also include patient satisfaction, grip strength and late complications.

The DASH questionnaire is used to assess global disability of the upper limb. The questionnaire is a self-reported 30 item questionnaire that patients rate difficulty and interference with daily life on a 5-point Likert scale. The DASH is scored using the formula = ([(sum of n responses)/n] -1) where n represents the number of completed items. The score on both test ranges from 0 (no disability) to 100 (most severe disability).

The PRWE is a wrist specific questionnaire that has 15-items designed to measure wrist pain and disability in activities of daily living. The pain subscale contains 5 items each of which is further rated from 1 to 10. The function subscale contains a total of 10 items which are further divided into 2 sections: specific activities (6 items) and usual activities (4 items). Both subscales are scored out of 50, and the total score is the sum of the two scores, where 100 is the poorest possible outcome.

Grip strength will be recorded from three attempts alternating between left and right hands have using Jamar digital dynamometer in position 2.

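### DASH and PRWE are to be compared by ANOVA of change scores although baseline scores are collected; adjusting for baseline would gain precision at no cost (minor, secondary outcomes only)

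*Protocol article*

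**What the plan says.** Three statements in the protocol article bear on this.

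- Statistical analysis: "Continuous secondary outcomes will be analysed by ANOVA". No covariate is mentioned.
- Secondary outcomes: "Secondary outcomes will include changes from baseline DASH and PRWE".
- Baseline data, on the pre-operative assessment: "Patient reported outcome measures including the DASH and the PRWE will also be administered".

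Read together, the stated plan for these two questionnaires is an ANOVA of change scores with the baseline value in hand. The abstract places the assessments at 1, 2 and 5 years. Randomisation is stratified by surgeon (Trial design; Randomisation and blinding).

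Grip strength is treated differently. It is listed as an outcome ("Secondary outcomes will also include patient satisfaction, grip strength and late complications") but not defined as a change, and the text records no pre-operative grip measurement.

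The Statistical analysis section also says "This study is not powered to discriminate between treatments in terms of DASH and PRWE", with the reason "given the MCID (95% confidence interval) is 10 [5–15] and 14 (8–20), respectively". It gives no SD, correlation or power figure for either score.

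**The concern.** Subtracting the baseline score gives it a fixed weight of one. Unless the regression of follow-up on baseline has a slope of exactly one, that weight is wrong and adds noise to the treatment comparison. ANCOVA estimates the weight from the data. It also removes the part of a chance baseline imbalance that a change score over- or under-corrects, which matters with about 48 evaluable patients per arm.

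What is at stake is the width of the confidence intervals for DASH and PRWE. Comparing patient-reported outcomes is one of the specific aims listed under Objectives, and the article itself warns that the trial is weak for these scores. Giving up precision that the collected data would supply is therefore hard to justify.

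**Working it through.** **Inputs from the article.** Total 120, 1:1 allocation, alpha 0.05, 20% dropout (Sample size; Randomisation and blinding). MCID 10 for DASH (95% CI 5 to 15) and 14 for PRWE (8 to 20) (Statistical analysis). Evaluable per arm: 120 × 0.8 / 2 = 48.

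**Assumptions, because the article gives no value.** Two-sided test; SD of the score; correlation rho between baseline and follow-up; 48 per arm at the visit analysed.

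**Plan's own figure.** None exists for DASH or PRWE. The 120 was derived for CMCJ complications without stated rates, so it can be neither reproduced nor refuted. It is used here only to obtain 48 per arm.

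**Step 1: relative variance of the treatment effect.** With equal SDs at baseline and follow-up:

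- follow-up score alone: 1
- change score: 2(1 − rho)
- ANCOVA: 1 − rho²

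ANCOVA against change is (1 − rho²) / [2(1 − rho)] = (1 + rho)/2. ANCOVA against the follow-up score is 1 − rho².

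| rho | change | ANCOVA | ANCOVA / change | ANCOVA / follow-up score |
|---|---|---|---|---|
| 0.3 | 1.40 | 0.91 | 0.65 | 0.91 |
| 0.5 | 1.00 | 0.75 | 0.75 | 0.75 |
| 0.7 | 0.60 | 0.51 | 0.85 | 0.51 |
| 0.8 | 0.40 | 0.36 | 0.90 | 0.36 |

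Neither ratio exceeds 1, apart from the one degree of freedom spent on the covariate. Equal SDs are not essential to that ordering. With SDs s0 and s1, change-score variance minus ANCOVA variance is (s0² + s1² − 2·rho·s0·s1) − s1²(1 − rho²) = (s0 − rho·s1)², which cannot be negative.

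**Step 2: illustration for DASH.** Difference 10, assumed SD 20, 48 per arm, normal approximation: power = Φ(10 / [20·√v·√(2/48)] − 1.96), where v is the relative variance.

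- rho 0.5, change (v = 1): 10 / 4.08 = 2.449; Φ(0.489) = 69%.
- rho 0.5, ANCOVA (v = 0.75): 2.449 / 0.866 = 2.828; Φ(0.868) = 81%.
- rho 0.3: change 54%, ANCOVA 73%.
- rho 0.7: change 88%, ANCOVA 93%.

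For 80% power at SD 20 and rho 0.5, change scores need 63 per arm and ANCOVA needs 48.

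**Step 3: the power sentence.** For a comparison with relative variance 1, 80% power at 48 per arm needs SD ≤ difference / [(1.96 + 0.8416)·√(2/48)] = difference / 0.572.

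- DASH differences of 5, 10 and 15: SD ≤ 8.7, 17.5 and 26.2.
- PRWE differences of 8, 14 and 20: SD ≤ 14.0, 24.5 and 35.0.

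Whether the sentence is true therefore depends on an SD that the article does not state.

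**The case against.** The strongest reply is that one condensed sentence in an article does not exclude covariates, and that an unseen analysis plan may name them. That is fair as to certainty. Still, the article does fix a method and an outcome form, and the combination it publishes is the less efficient one. Changing the sentence is a specific improvement, not a complaint about missing detail.

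The second reply is that change-score ANOVA is valid. This stands in full: under randomisation it is unbiased, and regression to the mean affects both arms alike in expectation. The point concerns efficiency only.

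A reader might be tempted to go further in four ways that the article does not support.

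- **That grip wastes a baseline value.** No pre-operative grip appears in the text, and the schedule in Fig. 1 could not be read for this review. Opposite-hand grip is documented only as part of the outcome measurement, so it cannot be assumed to be a baseline covariate.
- **That the three visits will be analysed separately, ignoring their correlation.** The article does not say how visits are handled.
- **That adjustment brings the detectable difference inside the MCID.** At SD 20 and rho 0.5 it does fall from 0.572 × 20 = 11.4 to 11.4 × 0.866 = 9.9. At that SD, however, the crossing of 10 occurs only for rho between about 0.49 and 0.62. At rho 0.5 there is no crossing at SD 15 (8.6 to 7.4) or SD 25 (14.3 to 12.4).
- **That the power disclaimer is wrong.** It is under-supported, but at the lower MCID limits it would need SDs of at most 8.7 and 14.0 to be false. It is a caution, and no design figure rests on it.

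**Conclusion.** The point holds as a minor, cost-free improvement for DASH and PRWE. Using the baseline score as a covariate is never less precise than the stated change-score ANOVA, apart from one degree of freedom. The variance reduction against change scores is 35%, 25% and 15% at rho of 0.3, 0.5 and 0.7, and 10% at 0.8. If raw follow-up scores were analysed instead, it would be 9%, 25% and 49% at rho of 0.3, 0.5 and 0.7.

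The ordering of the methods does not depend on the assumptions. The size of the gain depends on rho, and the power figures depend also on SD, a two-sided test and 48 evaluable per arm. The primary outcome, the sample size of 120 and the validity of the secondary comparisons are untouched.

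**What to change.** In Statistical analysis, replace the ANOVA sentence for these scores by a statement along these lines: DASH and PRWE at 1, 2 and 5 years will be compared between arms by ANCOVA at each visit, or by a mixed model for repeated measures with arm, visit and arm-by-visit terms, with the baseline score and surgeon (the stratification factor) as covariates. Mean change may still be reported descriptively. At a single visit, ANCOVA gives the same treatment effect whether the response is the change or the follow-up score, so the outcome definition need not be altered.

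Apply the same model to grip strength only if it is measured before surgery; if it is, say so in Baseline data.

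Optionally, support the power sentence with an assumed SD and the resulting detectable difference at 48 per arm.

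The cost is wording only. DASH and PRWE baselines are already collected, and no visit, measurement or patient is added. The change should be dated before anyone sees outcome data by arm.

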## Discussion

The objective of this trial is to determine whether or not the CMCJ should be fused in TWA. This study will also determine the need for hardware removal and give an insight into how CMCJ is loaded following TWA by assessing the development of problems at this site.

We choose a simple study design with simple outcomes. The primary outcome is complications within 1 year of surgery. TWA are reported to unite at approximately 12 weeks and it is generally accepted that pain and function stabilise by 12 months. We therefore expect that most cases of non-union, hardware failure and soft tissue irritation will be evident by 12 months.

The secondary outcomes that we choose to examine include late complications (up to 5 years), DASH and PRWE. Nagy reported that union of the CMCJ is hard to determine, especially with hardware in situ [10]. Reigstad reported a significant number of late complications in a cohort of TWA for non-inflammatory wrist arthritis followed up for a mean of 11 years [15]. We therefore felt it important to extend the follow up period to observe undetected CMCJ non-union, indicated hardware breakage and development of CMCJ pain due to extended periods of abnormal load on the joint, as well as other complications which may be undetected within 12 months of TWA.

This randomised clinical trial will provide insight into the outcomes of TWA and may facilitate recommendation of a superior surgical method. We plan to begin recruitment of participants in early 2021.

## Data Availability

Not applicable.

## Abbreviations

ANOVA: Analysis of variance
CMCJ: Carpometcarpal joint
CT: Computer tomography
DASH: Disabilities of the arm shoulder and hand
IBRA: International Bone Research Association
MCID: Minimal important difference
PRWE: Patient-rated wrist evaluation
SPIRIT: Standard Protocol Items: Recommendations for Interventional Trials
TWA: Total wrist arthrodesis
